## 3.4 Sample size calculation

The statistical power to detect a difference of at least 50 mg/L in serum apo A-I concentrations between the experimental and control period is over 80%, when 45 subjects are included at P=0.05. For the calculations, a within-subject variability of 120 mg/L in serum apo A-I concentrations is used. As the expected drop-out rate is 10%, a total of fifty men and women will be recruited.

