**Primary research question:**

What is the effect of resveratrol supplementation on serum apoA-I concentrations in men and women with low HDL-C concentrations?

*Major null hypothesis, H_0_:*

As compared with control capsules, a daily intake of two capsules each containing 75 mg resveratrol for 4 weeks does not change serum apoA-I concentrations in subjects with low HDL-C concentrations.

*Major alternate hypothesis, H_a_:*

As compared with control capsules, a daily intake of two capsules each containing 75 mg resveratrol for 4 weeks does change serum apoA-I concentrations in subjects with low HDL-C concentrations.

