## 7.2 Univariate analysis

For statistical analyses, the differences in effect of the placebo capsules and experimental capsules will be determined by comparing the changes between absolute concentrations as measured after the 4-week experimental period and the 4-week placebo period by using a paired T-test. Period and carry-over effects will be analyzed as described [21]. ANCOVA will be performed if baseline values are statistically different between the groups. If available, values of days 25 and 28 will be averaged to reduce within-subject variability.

Postprandial effects will be compared by using ANOVA with time, diet and subject number as factors. In all cases, a P-value <0.05 is considered to be statistically significant.

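### Section 3.4 does not say which standard deviation the 120 mg/L is, and the claimed power above 80% with 45 subjects does not follow from the inputs it states

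*Protocol*

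**What the plan says.** Section 3.4 of the protocol gives the sample size for the primary endpoint. The trial is sized to "detect a difference of at least 50 mg/L in serum apo A-I concentrations between the experimental and control period". For this target, the section claims that the power "is over 80%, when 45 subjects are included at P=0.05". On the variability it says only that "a within-subject variability of 120 mg/L in serum apo A-I concentrations is used". It then allows for 10% drop-out and recruits fifty. It does not mention averaging, the formula or the sidedness.

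Section 7.2 fixes the primary comparison as one between the end of "the 4-week experimental period and the 4-week placebo period by using a paired T-test". It adds that, where both are available, "values of days 25 and 28 will be averaged to reduce within-subject variability". The significance rule is "In all cases, a P-value <0.05 is considered to be statistically significant". The alternative hypothesis in section 2 is non-directional: resveratrol "does change serum apoA-I concentrations in subjects with low HDL-C concentrations". The test is therefore two-sided.

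**The concern.** A paired t-test works on the difference between two period values in the same subject, so its power depends on the SD of that difference. A within-subject SD describes the scatter of one person's repeated values around that person's own mean. The difference of two such values has an SD larger by a factor of sqrt(2).

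The protocol's own usage points to the second quantity. Section 7.2 averages two days to lower within-subject variability, and section 5.1 gives the same reason for holding two screening visits. In both places the term means variation between repeated measurements. Section 3.4 also attaches the 120 mg/L to concentrations, not to differences. Yet the sample size of 45 appears only when 120 is treated as the SD of the difference. The term and the calculation do not match.

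Section 3.4 is the only justification for the size of the trial on its primary endpoint. A reader cannot tell from it whether the chance of detecting a 50 mg/L effect is about one half or about four fifths.

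**Working it through.** **Inputs.** Difference d = 50 mg/L, n = 45, variability 120 mg/L and 10% drop-out (section 3.4); paired t-test and alpha 0.05 (section 7.2); two-sided, from the non-directional hypothesis (section 2).

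**Formulas.** Let S be the SD of the paired difference.
- Normal approximation: n = ((1.960 + 0.842) × S / d)².
- Exact t: noncentrality = d × sqrt(n) / S, with n − 1 = 44 degrees of freedom, two-sided 0.05.

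**Step 1. Reproduce the protocol's 45.** Put S = 120: n = (2.802 × 120/50)² = 45.2. The drop-out step also reproduces: 45/0.90 = 50. So 45 corresponds to S = 120 and 80% power under the normal formula.

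**Step 2. Power at n = 45 with S = 120.** Noncentrality = 50 × 6.708/120 = 2.795.
- Normal approximation: 79.8%.
- Exact t: 78.0%. For 80%, 48 completers are needed, and the difference detectable with 80% power at n = 45 is 51.2 mg/L.
- For 80% at n = 45, S must be no more than 117.1 (exact t) or 119.7 (normal).

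**Step 3. Power if 120 is the within-subject SD of a period value.** S = 120 × sqrt(2) = 169.7; noncentrality = 50 × 6.708/169.7 = 1.976.
- Exact t: 48.9%. Normal approximation: 50.7%.
- For 80%, 93 completers are needed; the detectable difference at n = 45 is about 72 mg/L.

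**Step 4. Effect of averaging days 25 and 28.** The protocol gives no correlation between the two days, so r below is an assumption, shown as a range. It is the correlation of the within-subject deviations in the first case and of the paired differences in the second.

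- Case A: 120 is a single-sample within-subject SD. Then S = 120 × sqrt(1 + r).
- Case B: 120 is the SD of a difference between single samples. Then S = 120 × sqrt((1 + r)/2).

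| r (assumed) | Case A: S | Case A: power | Case B: S | Case B: power |
|---|---|---|---|---|
| 0 | 120.0 | 78.0% | 84.9 | 97.2% |
| 0.25 | 134.2 | 68.6% | 94.9 | 93.3% |
| 0.5 | 147.0 | 60.7% | 103.9 | 88.4% |
| 0.75 | 158.7 | 54.3% | 112.2 | 83.2% |
| 0.9 | 165.4 | 50.9% | 117.0 | 80.1% |
| 1 | 169.7 | 48.9% | 120.0 | 78.0% |

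All powers are two-sided exact t at n = 45. Case A never reaches 80%. Case B stays above 80% for r up to about 0.9.

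**The case against.** The strongest reply is that the number reproduces. With 120 as the SD of the paired difference, the standard formula gives 45.2, and a shortfall of 0.2 points (normal) or 2 points (exact t) is a matter of formula and rounding. The protocol's own 45 fits this reading, whereas the other reading would need 93. The source of the 120 is not in the document, so nobody can show that a factor of sqrt(2) was left out. This stands: a reader might infer a proven arithmetic error and a trial with 49% power, and the document supports neither as a fact. The 49% is conditional on the literal wording.

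A reader might also infer that 78% is the ceiling. It is not. If 120 is the SD of a difference between single samples, the averaging in section 7.2 lifts power to 83–93% for correlations of 0.75 down to 0.25. The claim of more than 80% could then be true, although section 3.4 does not make that argument.

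Two other rescues do not work. A one-sided test with S = 120 would give 86.6%, but the hypotheses are two-sided. Fifty completers would give 82.3%, but section 3.4 ties its claim to 45 and expects to lose 10%, and section 5.4 rules out replacement.

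Finally, low planned power does not by itself settle what a null result would mean. Whether 50 mg/L is excluded depends on the observed confidence interval.

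**Conclusion.** The point holds as a claim that the stated inputs do not support, resting on an undefined variance term. Without averaging, the two-sided paired t-test at n = 45 has 48.9% power if 120 mg/L is the within-subject SD of a period value, and 78.0% (79.8% by normal approximation) if it is the SD of the paired difference. Neither exceeds 80%; the first misses by a wide margin and the second only marginally.

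With averaging, the range is 49–78% in Case A, while Case B exceeds 80% for correlations up to about 0.9. Those ranges rest on assumed correlations and on both days being available.

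The documents do not show which reading is the true one. The finding is therefore not that the trial is underpowered, but that section 3.4 leaves the power of the primary comparison anywhere from about one half to well above 80%, while stating one favourable figure.

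**What to change.** Rewrite the paragraph in section 3.4 to:

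- state whether 120 mg/L is the within-subject SD of a single sample, the within-subject SD of a period mean, or the SD of the paired difference, and whether averaging days 25 and 28 is already included in it;
- carry out the calculation with the SD of the paired difference, which is sqrt(2) times a within-subject SD of the period value, giving any between-day correlation assumed;
- replace the claim of more than 80% with the resulting two-sided paired t-test power at n = 45;
- add the difference detectable with 80% power at n = 45 (about 51 mg/L if the SD of the difference is 120, about 72 mg/L if it is 169.7).

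The cost is one paragraph and possibly a less favourable stated power. No extra enrolment is needed, and the design and the test stay as they are.

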# 4. TREATMENT OF SUBJECTS

For the first four weeks of the study, subjects will be randomly allocated to either the experimental or the control group. Capsules should be taken twice a day, i.e. one capsule at lunch and one capsule at dinner. After a 4 weeks of wash-out period, during which no capsules should be taken, regimes will be crossed over. Experimental capsules will contain 75 mg resveratrol, placebo capsules will contain 58 mg cellulose. Thus, either 150 mg resveratrol or 116 mg cellulose will be consumed each day.

## 4.1. Investigational Product and supplementation regimen

### 4.1.1 Investigational Product

#### 4.1.1.1 Investigational product name and formulation

Resveratrol will be provided as trans-Resveratrol (resVida^TM^), provided as capsules (75 mg). DSM Nutritional Products Ltd (DNP) will provide the study investigational product (resVida™) and placebo capsules.

- Product name: resVida™

- Active compound: *trans*-Resveratrol

- Formulation: 99% pure, crystalline.

- Lot: RC0908009

- Capsules: 75 mg active compound/capsule

#### 4.1.1.2 Packaging and labelling

The product will be packaged and labelled by the principle investigators.

The label on the investigational product bears the following information:

- Investigator name, address, phone number
- DSM Nutritional Products Ltd.
- Dosage form, route of administration, quantity of dosage units
- Protocol number
- Investigational product Batch number
- Subject ID
- Storage conditions
- Keep out of reach of children
- For investigational use only
- Directions of use
- Expiration date

#### 4.1.1.3 Handling and storage conditions

The study capsules will be distributed into study bottles and dispensed to study subjects. The capsules will be stored in the dark at room temperature in room 3.247, [name], Maastricht.

### 4.1.2 Randomization, blinding and treatment allocation

The subjects will receive the two types of capsules in random order, based upon a computer-generated table with random numbers. For this, a categorical list in logical order will be created by an independent person. This list will include the two interventions for each subject. After addition of a computer-generated list of random numbers, the list will be sorted by subject number and random number, resulting in a randomized list of treatment allocation. To blind the researchers and the subjects, the capsules will be coded. The randomization code will be broken after statistical analyses are completed.

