Before screening, subjects will be informed about the procedures and informed consent will be obtained. Subjects will be informed about their results and advised to consult their general practitioner when values are outside normal ranges. When a subject does not want to be informed about the results, it is not possible to participate in this study. Subjects that fulfil all inclusion criteria and are willing to participate will be randomly allocated to receive either the placebo capsules or the experimental capsules for a period of four weeks. This period will be followed by a four-week wash-out period, after which regimes will be crossed over. In this way variation due to drift of variables with time is eliminated. Possible residual effects will be minimized by a washout period of at least four weeks between two periods. The placebo and experimental capsules have to be consumed at lunch and dinner, and will be coded to assure blindness of the investigator and participants. Experimental capsules will each contain 75 mg resveratrol and placebo capsules 58 mg cellulose (**Appendix 1**). During each visit, subjects will be supplied with the amount of capsules that is sufficient for the next visit. Leftovers should be returned and counted.

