# 9. ADMINISTRATIVE ASPECTS AND PUBLICATION

## 9.1 Handling and storage of data and documents

Before the start of the screening, subjects will be assigned a random number that will not change during the study. This number is linked with the name, address, date of birth, and telephone number of the subject in a password-protected file. Except for the technicians and the dietician, only members of the project team can access this file. For all other purposes, the random number will be used for subject identification.

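### The randomisation in Section 4.1.2 draws each subject's sequence independently, so the 25/25 split in Table 1 is reached in only about 11% of trials, and the stated paired t-test has no period term to absorb the imbalance

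*Protocol*

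**What the plan says.** Protocol Section 4.1.2 states the aim: "The subjects will receive the two types of capsules in random order, based upon a computer-generated table with random numbers". An independent person first prepares an ordered list, and "This list will include the two interventions for each subject". Random numbers are added, after which "the list will be sorted by subject number and random number, resulting in a randomized list of treatment allocation". The protocol mentions no block, stratum or limit on the sequence totals.

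Table 1 (Section 3, Study design) shows two sequence groups, each with N=25. Section 3.4 gives the total: "a total of fifty men and women will be recruited". The text after Table 1 explains what crossing over achieves: "In this way variation due to drift of variables with time is eliminated".

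Section 7.2 compares values after "the 4-week experimental period and the 4-week placebo period by using a paired T-test". It then adds: "Period and carry-over effects will be analyzed as described [21" (the number refers to the reference list). It does not say that the treatment estimate is adjusted for period. Reference 21 is listed as a grape-polyphenol study in women and is also cited for the wash-out. The protocol itself sets out no method for the period analysis.

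**The concern.** Table 1 presents equal sequences as a feature of the design, but Section 4.1.2 describes a procedure that does not produce them except by chance. The difference matters because of the analysis. A mean of within-subject differences cancels a shift between period 1 and period 2 only when equal numbers of subjects take the treatments in each order. With unequal sequences, resveratrol and placebo are not spread equally over the two periods, and part of any shift is counted as treatment effect. The statement that drift is eliminated then depends either on balance, which the list does not guarantee, or on a period term, which the primary test does not state.

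**Working it through.** **Inputs.** N = 50 recruited, 45 evaluable, 10% drop-out, target difference 50 mg/L, variability 120 mg/L (all Section 3.4); 25 per sequence (Table 1); list structure and sort keys (Section 4.1.2). The protocol gives no figure for drift in apoA-I, so 10, 25 and 50 mg/L are assumed below as a range.

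**The plan's own figures.** 45/0.90 = 50 reproduces the recruitment total. Under Section 4.1.2 the expected size of each sequence is 50 × 0.5 = 25. Table 1 is therefore reproduced as an average, not as a fixed allocation.

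**What the sort does.** There are two rows per subject. Sorting by subject number keeps the two rows together, and the random number then decides which comes first. Each subject has either order with probability 1/2, independently of the others. With one row per subject, sorting first by subject number would leave the random number without effect, so the two-row reading is the one under which the procedure randomises anything.

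**Distribution of the split.** n1 ~ Binomial(50, 0.5).
- P(n1 = 25) = C(50,25)/2^50 = 0.112. Simulating the literal sort 20,000 times gave 0.108.
- SD of n1 = √(50 × 0.25) = 3.54; the 2.5% and 97.5% quantiles are 18 and 32.
- P(20/30 or worse) = 0.203; P(18/32 or worse) = 0.065.
- Mean absolute difference between the groups = 5.6 subjects.

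**Effect on the paired estimate.** Let τ be the treatment effect and π the shift from period 1 to period 2. A resveratrol-first subject contributes τ − π, and a placebo-first subject contributes τ + π. The unadjusted mean is

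τ + π × (n2 − n1)/N.

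The share of π that enters is 10/50 = 20% at 20/30 and 14/50 = 28% at 18/32.

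| Assumed π (mg/L) | Shift at 20/30 | Shift at 18/32 |
| --- | --- | --- |
| 10 | 2 | 2.8 |
| 25 | 5 | 7 |
| 50 | 10 | 14 |

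**Scale.** If 120 mg/L is the SD of the paired difference, SE = 120/√50 = 17.0 mg/L. A 5 mg/L shift is then 5/17 = 0.3 SE, or 5/50 = 10% of the target difference. If 120 mg/L is instead the SD of a single value within a subject, the SD of the difference is 120 × √2 = 169.7 and SE = 169.7/√50 = 24 mg/L, so the same shift is a smaller fraction.

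**Cost of imbalance with a period term.** The efficiency relative to 25/25 is 4·n1·n2/N². At 20/30 this is 4 × 20 × 30/2500 = 0.96; at 18/32 it is 0.92. The average over the binomial distribution is 0.98.

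**The case against.** Simple randomisation is a valid method, and N=25 in Table 1 can be read as the expected split. Because the draws are independent, the shift averages zero over randomisations, and the period effect is already contained in the observed SD of the differences. In 200,000 simulated trials (N = 50, SD of the difference 120 mg/L, unadjusted paired t-test), type I error stayed at about 5% with drifts of 25 and 50 mg/L. Forcing 25/25 with the same test made it conservative (4.5% and 3.4%) and raised power by less than one point at 25 mg/L and less than two at 50 mg/L. All of this stands. A reader might infer that the allocation is biased or the test invalid, and the documents do not support that. What remains is a conditional shift: the trial is run once, with one realised split.

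A reader might also infer that screen failures distort the allocation, because of Section 9.1: "Before the start of the screening, subjects will be assigned a random number that will not change during the study". That does not hold for the procedure described. Removing subjects from a set of independent draws leaves independent draws, and Section 4.1.2 does not say that its subject number is the one given before screening. The point matters only once a balanced list is used.

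Large drift should not be inferred either. The seasonal span (October to June) and the ban on wine, grapes and berries make some drift conceivable. But the ban starts two weeks before the study and covers both periods, so the compared values lie about 6 and 14 weeks into it.

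Finally, Section 7.2 does promise an analysis of period effects, and a separate analysis plan may specify adjustment. The protocol as written leaves this open. A balanced list alone would not settle it: Section 5.4 rules out replacement, and 45 completers cannot divide equally.

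**Conclusion.** The point holds as a mismatch with modest consequences. Section 4.1.2 delivers the split in Table 1 in 11.2% of trials, with a central 95% range of 18 to 32 and a 20% chance of 20/30 or worse. The claim that time drift is eliminated does not hold for an unadjusted paired t-test when the sequences are unequal: 20% of any period shift enters the estimate at 20/30. Under assumed drifts of 10 to 50 mg/L that is 2 to 10 mg/L, against a standard error of about 17 mg/L. These figures rest on the two-row reading of the list, on all 50 subjects being analysed, on 120 mg/L as the SD of the paired difference, and on drift values the documents do not supply. The conclusion is about a given trial's estimate, not about average bias or type I error. The remedy costs almost nothing, so the change is worth making.

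**What to change.** 1. In Section 4.1.2, replace the within-subject sort by a list of 50 sequences, 25 resveratrol-first and 25 placebo-first, generated by the same independent person in permuted blocks whose sizes are concealed from the study team.
2. Assign the next entry only after eligibility has been confirmed, and do not key the list to the number given before screening, so that screen failures do not use up entries of a balanced list.
3. In Section 7.2, include period in the primary treatment comparison. This also handles imbalance from drop-outs who are not replaced, and removes the period effect from the residual variance.
4. Reword the statement in Section 3 so that removal of drift rests on the period-adjusted comparison.

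If simple randomisation is kept, describe the 25/25 in Table 1 as the expected split and still make change 3.

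The cost is a different list and one degree of freedom. The coded capsules and the visit schedule stay as they are.

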### 4.1.3 Supplementation regimen

#### 4.1.3.1 Rationale for dose selection

For the product resVida^TM^ the maximal recommended daily dosage in humans is 150 mg (investigator brochure DSM page 33). Therefore, we have chosen to supplement the subjects with a dose of 150 mg daily, spread out over doses of 75 mg twice a day with lunch and diner, this because the bioavailability of resveratrol is rather low (23). Detailed information on resVida^TM^ can be found in the “investigator brochure” **(Appendix 2)** enclosed with the protocol) supplied by DSM, which contains general information on resVida^TM^ (investigator brochure page 5-8), information on toxicology, pharmacokinetics, and metabolism of resVida^TM^ in animals (investigator brochure page 9-26), and the effects of resVida^TM^ supplementation in humans (metabolism, safety and pharmacokinetics) (investigator brochure page 28-33). The brochure is composed of mixture of research performed within DSM itself, and peer-reviewed scientific articles.

#### 4.1.3.2 Dosage regimen

Daily intake of two capsules at lunch and dinner each containing 75 mg resveratrol (=150 mg resveratrol per day) or placebo for 4 weeks.

First intake first period: on day 0 after the measurements and blood sampling

4-weeks supplementation until day 27

Last intake first period: day 27 evening

First intake second period: on day 56 after the measurements and blood sampling

4-weeks supplementation until day 83

Last intake second period: day 83 evening

No intake on the days when retinal images are taken (last week of each experimental period) and the postprandial tests (day 28 and day 84) are performed.

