**Nature and extent of the burden and risks associated with participation, benefit and group relatedness**: Before the study, subjects will be screened to determine eligibility during two visits of respectively 15 and 10 minutes. During these visits, body weight, height and blood pressure will be measured. In addition, a venous blood sample (5.5 mL at each occasion) will be drawn. During the study, subjects will receive the control and resveratrol capsules in random order. At days 1, 25, and 28 of each 4 wk experimental period, a fasting blood sample will be drawn (2 x 10 mL and 4 x 16.5 mL). In addition, a 4 hr postprandial test will be performed at day 28 of each experimental period. For this, subjects will receive two muffins and 300 mL low-fat milk, and an additional 8 blood samples will be taken (80 mL at each test). Thus, in total 257 mL blood will be drawn. Before and after each postprandial test, two FMD (including an ECG) and two PWV measurements will be performed. During the last week of each intervention period, a retinal image will be taken on a separate occasion. Subjects will be asked to fill out a food frequency questionnaire two times and to keep a study-diary throughout 12 weeks. On rare occasions, blood sampling might cause bruises or hematoma. Total time investment for the subjects will be approximately 16 hours.

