**Duration of the study**

It is projected that the study will start October 1, 2010. It is expected that the last subject will finish the study June 30, 2011.

Each subject will be involved in the study for 14 weeks:

- 1-2 weeks screening before enrolment
- First period: 4 weeks
- Wash-out period: 4 weeks (21, 22)
- Second period: 4 weeks

Table 1: Experimental design

|  | Screening | | Intervention period | | | Wash-out period | Intervention period | | |
| --- | --- | --- | --- | --- | --- | --- | --- | --- | --- |
| Group 1 (N=25) |  | | Experimental capsules | | |  | Placebo capsules | | |
| Group 2 (N=25) |  |  | Placebo capsules | | |  | Experimental capsules | | |
| Week |  | | 1 | 4 | | 4 weeks | 9 | 12 | |
| Day |  |  | 0 | 25 | 28 |  | 56 | 81 | 84 |
| Visit | -2 | -1 | 1 | 2 | 3 |  | 4 | 5 | 6 |
| Blood sampling | X | X | X | X | X |  | X | X | X |
| Postprandial test |  |  |  |  | X |  |  |  | X |
| Flow mediated dilation, including ECG |  |  |  |  | XX |  |  |  | XX |
| Pulse wave velocity |  |  |  |  | XX |  |  |  | XX |
| Retinal images * |  |  |  | X | |  |  | X | |
| Body weight | X | X | X | X | X |  | X | X | X |
| Height | X |  |  |  |  |  |  |  |  |
| Blood pressure,  heart rate | X | X | X | X | X |  | X | X | X |
| Capsule count |  |  |  | X | X |  |  | X | X |
| Food intake |  |  |  |  | X |  |  |  | X |
| Study diary |  |  | During total study period |  |  |  |  |  |  |
| AE reporting |  |  | During total study period | | | | | | |

* At an extra visit during the last week of each experimental period

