During the study, subjects will record in diaries any signs of illness, medication used, menstrual phase and any deviations from the protocol. Subjects are asked not to change their dietary habits, except for stopping the use of resveratrol-containing products during the study. Subjects will receive a list in which the resveratrol-containing products are stated, examples are wine, grapes and berries. Furthermore, subjects will be asked to maintain their level of physical exercise and use of oral contraceptives. At the end of each intervention period, food intake will be assessed by a validated food frequency questionnaire. Fasting blood samples will be drawn before the start of the study (day 0), twice in week 4 (days 25 and 28), after 8 weeks (day 56) and twice at the end of the study (days 81 and 84). FMD and PWV measurements will be performed at the end of each four-week intervention period (days 28 and 84), before and 4 hours after a standardized fat-load. During these days, blood will be sampled as indicated in figure 1 and as further explained in paragraph 6.2. Furthermore, retinal images will be made during the last week of each experimental period (see paragraph 6.3.2 and 6.3.3). Body-weight, height, blood pressure and ECG will be recorded as indicated in Table 1.

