#### 5.2.5.5 Compliance

Compliance to the study protocol will be checked by capsule count and by analyzing plasma samples on the intake of resveratrol and its metabolites at days 0, 25, 28, and 56, 81, and 84.

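### The retinal-imaging visit is not kept off the day before an end-of-period blood draw, so one of the two averaged samples may follow a capsule-free day

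*Protocol*

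**What the plan says.** Section 4.1.3.2 (Dosage regimen) contains two relevant lines. One withholds capsules around imaging: "No intake on the days when retinal images are taken (last week of each experimental period", and likewise on the postprandial test days. The other fixes the end of dosing: "Last intake first period: day 27 evening", with day 83 evening as the counterpart in period 2.

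The imaging day is never fixed. The Table 1 footnote in the Study design section has it "At an extra visit during the last week of each experimental period", and the Summary says "During the last week of each intervention period, a retinal image will be taken on a separate occasion".

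The end-of-period fasting samples are fixed: "twice in week 4 (days 25 and 28") in period 1 and "twice at the end of the study (days 81 and 84") in period 2. They serve two purposes:
- **Analysis.** Section 7.2 says that, where available, "values of days 25 and 28 will be averaged to reduce within-subject variability". Section 5.2.1 makes fasting serum apoA-I the main endpoint.
- **Compliance.** Besides counting returned capsules, the section headed 5.2.5.5 relies on this laboratory check: "analyzing plasma samples on the intake of resveratrol and its metabolites at days 0, 25, 28, and 56, 81, and 84".

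**The concern.** The imaging day is a day without capsules, and nothing in the text keeps it off the eve of a blood draw. A subject imaged the day before a draw would give that sample after a full capsule-free day, while the other sample in the pair would follow normal dosing. The protocol plans to average the two to reduce variability, yet leaves the interval since the last capsule free to differ between them and between subjects.

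The plasma resveratrol measurement is the most exposed. It is meant to show whether capsules were taken, and a value drawn after a scheduled skipped day may be low in a subject who followed every instruction. Nothing in the protocol asks for the last-capsule time at the draw, so the two explanations could not be told apart from that value alone.

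**Working it through.** **Inputs**
- Capsules are taken at lunch and dinner (section 4).
- The overnight fast before a test day starts at 8 pm and arrival is around 8 am (sections 4.2 and 5.1).
- Dosing runs from day 0 to day 27 and from day 56 to day 83 (section 4.1.3.2).
- End-of-period draws are on days 25 and 28, and on days 81 and 84.
- Assumptions: the dinner capsule is taken between 18:00 and 20:00, the upper bound being the start of the fast, and every end-of-period draw is at 08:00. The protocol states the arrival time for the test day. For day 25 it asks only that venipunctures be at the same time of day as far as possible.

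**Formula**

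Interval = 08:00 on the draw day minus the dinner time on the last dosed day before it.

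- Dosed the evening before: from 20:00 to 08:00 is 12 h, and from 18:00 to 08:00 is 14 h.
- Evening before skipped: add 24 h, giving 36 h to 38 h.

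**Result for each possible imaging day in period 1** (add 56 days for period 2)

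| Imaging day | Interval at day 25 | Interval at day 28 |
|---|---|---|
| 21, 22, 23 | 12-14 h | 12-14 h |
| 24 | **36-38 h** | 12-14 h |
| 25, 26 | 12-14 h | 12-14 h |
| 27 | 12-14 h | **36-38 h** |
| 28 | 12-14 h | 12-14 h |

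Imaging on day 25 itself is harmless here, because the draw is in the morning and the withheld capsules are those of the following lunch and dinner.

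**Whether the text allows each affected day**
- *Day 24 (80).* It lies in the last week, and no line excludes it.
- *Day 27 (83).* It lies in the last week, so the Table 1 footnote admits it. With imaging that day no capsule may be taken, so the last intake cannot be that evening. The imaging window and the fixed last intake cannot both be honoured on that day.

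**Weight in the averaged value**

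Let Δ be the effect with usual dosing and f the unknown fraction of it lost at the affected sample. The averaged effect is [Δ + (1 − f)Δ]/2 = (1 − f/2)Δ, so averaging halves the loss. The documents give no half-life for resveratrol and no turnover for apoA-I, so f could lie anywhere from 0 to 1 and no value can be assigned. If the other sample of the pair is missing, the affected one stands alone and the halving is lost.

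**The case against.** Much of the case on the other side stands.

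- **Day 27 (83) may be excluded by implication.** The no-intake line and the fixed last intake can both be met if imaging never falls on that day. A reader might infer that the day-28 FMD, PWV and fat-load test could follow 36-38 h without product. That happens only if the last-intake line is broken, so it should not be presented as something the protocol freely permits. The implied exclusion is nowhere written where the visit is scheduled, though, and it does not cover day 24 (80).
- **A bias of the primary endpoint toward no effect is not shown.** A reader might infer it, because skipping a capsule matters only in the resveratrol period. It requires apoA-I to depend on intake in the preceding day. The documents give no kinetics, the hypothesis concerns four weeks of intake, and one skipped day is 2 of 28 × 2 = 56 capsules (3.6%). Such a bias is possible but cannot be sized.
- **The formal compliance rule is hardly touched.** Section 4.1.5 defines compliance as 80% of planned intake by pill count, and no plasma threshold is stated. The other end-of-period sample also keeps its usual interval. What remains is the interpretation of a single low plasma value.
- **No frequency of collisions can be given.** A reader might try to count working-day slots. The protocol states neither the visit weekdays nor how imaging slots are allotted, so such a count would rest on assumptions found nowhere in it.
- **The same imaging day in both periods is not needed.** Once draw-eve days are avoided, every blood-sample interval is 12-14 h, and matching the periods adds nothing for those samples.

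**Conclusion.** The point holds as a minor one. The protocol allows imaging on day 24 (80), which lengthens the interval from last capsule to the day-25 (81) sample by 24 h, from about 12-14 h to about 36-38 h. For day 27 (83), the imaging window in Table 1 and the dosing lines in section 4.1.3.2 are not aligned and must be reconciled. With one imaging visit, at most one of the two averaged samples per period is affected.

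The hours rest on the assumed dinner and draw times; the 24 h difference does not, provided those times are the same from day to day. Nothing in the documents supports a stated loss of effect on apoA-I. The firmest consequence is an ambiguous exposure check: a low resveratrol value may mean a scheduled skipped day or missed capsules.

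**What to change.** Reconcile the Table 1 footnote with section 4.1.3.2 by stating that the imaging visit does not fall on the day before an end-of-period blood draw, that is, not on days 24, 27, 80 or 83. Every end-of-period sample then comes about 12-14 h after the last scheduled capsule, under the timing assumptions above. This is a visit-scheduling statement and alters neither dosing line; the dosing rules themselves remain for the sponsor to settle.

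Also record the date and time of the last capsule at each draw, so that a low plasma value can be interpreted.

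The cost is one sentence, one extra field on the record form and fewer bookable slots at the ophthalmology clinic. Of the seven calendar days 21 to 27, five remain before weekends and clinic hours are considered. No visit is added.
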